## Abstract

**Background**: Despite clear evidence supporting the benefits of outpatient cardiac rehabilitation for acute coronary syndrome survivors, participation rates remain low. Many patients face person-level and system-level barriers for outpatient rehabilitation, and their motivation often wanes soon after discharge. Cardiopulmonary exercise testing provides individualized physiological information and may act as an external cue that enhances engagement, yet no randomized trial has evaluated whether announcing a scheduled test can influence rehabilitation attendance. **Methods**: This single-center, parallel-group, single-blind randomized controlled trial investigates whether informing patients during hospitalization that a cardiopulmonary exercise test will be conducted at their first rehabilitation visit increases early outpatient attendance. Patients with acute coronary syndrome are randomized 1:1 to receive either standard discharge education or the same education plus an exercise testing announcement. All other clinical care follows routine practice. The primary endpoint is completion of the first rehabilitation clinic visit within 30 days. Secondary outcomes include attending at least six rehabilitation sessions within 12 weeks, actual exercise testing completion, and any safety events. The analyses will follow the intention-to-treat principle and will use logistic regression and time-to-event models. The planned sample size is 200 participants.

## 1. Introduction

### 1.1. The Crucial Role of Cardiac Rehabilitation and the Implementation Gap

Cardiovascular diseases remain the leading global cause of death, accounting for more than 19 million deaths in 2022 [1]. Acute coronary syndrome (ACS) arises from the sudden disruption of an atherosclerotic plaque and may result in myocardial infarction or unstable angina [2]. Although advances in percutaneous coronary intervention and medical therapy have markedly improved short-term survival [3], many patients continue to experience limited long-term functional recovery and impaired quality of life [4].

Cardiac rehabilitation is a comprehensive secondary prevention intervention that includes exercise training, risk factor modification, and psychosocial support. Strong evidence from randomized trials and meta-analyses have shown that receiving cardiac rehabilitation reduces cardiovascular mortality, all-cause mortality, and re-hospitalization, along with improvements in exercise capacity and quality of life among ACS patients [5,6]. Guidelines from the American Heart Association (AHA), the American College of Cardiology (ACC), and the European Society of Cardiology (ESC) have recommended cardiac rehabilitation as a Class I intervention for eligible patients [7,8].

### 1.2. The Implementation Gap of Cardiac Rehabilitation

Despite this strong evidence, cardiac rehabilitation participation rates remain low. In many regions of the world, less than 20–30% of eligible patients attend outpatient cardiac rehabilitation, with even lower rates reported in parts of Asia [9,10,11]. In Taiwan, the actual completion rates of outpatient cardiac rehabilitation have been reported to be below 10% [12,13].

This persistent gap between proven efficacy and real-world practice raises important questions. Prior studies have proposed several patient-level obstacles, including insufficient understanding of cardiac rehabilitation, work or family obligations, transportation burden, and low perceived need for structured exercise [14,15]. System-level gaps such as inconsistent referral processes, lack of automatic referral pathways and staffing, and limited program capacity further contribute to low participation [16,17]. Psychosocial factors, including inadequate family support, anxiety, and persistent uncertainty following acute coronary events, also influence engagement, particularly among women and older adults [18,19].

Increasing attention has been directed toward alternative and non-traditional models of cardiac rehabilitation delivery, with recent literature emphasizing the importance of comprehensive and personalized approaches to address logistical, occupational, and motivational barriers associated with conventional rehabilitation programs [20,21]. Successful examples of cardiac rehabilitation implementation have been reported in highly structured clinical settings, where multidisciplinary teams and well-established referral and follow-up pathways enable high levels of patient engagement and program completion [22]. Automatic referral with liaison follow-up, nurse-led case management, structured education, financial incentives, mobile health applications, and text-messaging programs have each demonstrated varying degrees of success in promoting rehabilitation engagement [16,23,24,25,26,27]. However, many of these interventions depend on additional staffing, long-term funding, or specialized digital platforms, which limit widespread scaling, particularly in settings with constrained resources or low digital literacy [17,28,29]. Given these challenges, simple and universally applicable behavioral approaches that can be integrated into routine workflows are needed.

### 1.3. The Role and Clinical Importance of CPET

Cardiopulmonary exercise testing (CPET) is widely used in cardiovascular and sports medicine to assess functional capacity, identify exercise intolerance, and guide exercise prescription. It provides objective, individualized metrics such as peak oxygen uptake (peak VO_2_) and ventilatory efficiency (VE), which are strongly associated with prognosis in coronary artery disease and reflects the recovery of cardiopulmonary fitness [30,31]. Contemporary guidelines consistently endorse CPET as a valuable tool for risk stratification and for tailoring exercise training in cardiac rehabilitation programs [7,32]. Despite its central role in clinical evaluation, CPET has traditionally been used primarily for diagnostic clarification, risk assessment, and exercise prescription. Its function has rarely been considered beyond the physiological or diagnostic domain, and its potential influence on patient motivation or behavior has remained unexplored.

### 1.4. Behavioral Potential of CPET: Opportunities from a Health Psychology Perspective

Although CPET has been viewed mainly as a physiological test, theoretical perspectives from behavioral science suggest that its announcement and framing could have motivational value. The Health Information Seeking Behavior (HISB) model indicates that individuals who have experienced health uncertainty or vulnerability actively seek personalized health information, particularly when they expect actionable feedback [33,34]. For patients recovering from ACS, the prospect of receiving objective CPET results might trigger this information-seeking drive.

Similarly, the concept of a “teachable moment” suggests that acute health events temporarily heighten attention to risk and openness to change [35,36]. However, this heightened motivation declines soon after discharge. Announcing a forthcoming CPET may help to extend this motivational window by creating a personalized event linked directly to their recovery.

The Health Belief Model (HBM) further supports the possibility that CPET announcement may shape behavior. By emphasizing the need to evaluate cardiopulmonary function shortly after hospitalization, the announcement may enhance perceived susceptibility, reinforce the severity of the illness experience, highlight the benefit of rehabilitation for improving CPET outcomes, and act as a direct “cue to action” [37,38]. Together, these frameworks suggest that when framed deliberately, CPET could serve not only as a physiological assessment but also as a behavioral trigger.

### 1.5. Integrating Clinical and Behavioral Perspectives: Study Hypothesis

Building on these insights, the present study examines the potential of CPET beyond its conventional diagnostic role. We hypothesize that patients who are clearly informed about an upcoming CPET may exhibit stronger motivation to return for early outpatient rehabilitation. The trial is therefore designed to examine whether embedding this cue within routine discharge planning can meaningfully influence initial attendance and serve as an accessible, scalable strategy to address the persistent gap between guideline-recommended cardiac rehabilitation and actual participation.

## 2. Materials and Methods

### 2.1. Study Design and Setting

This is a prospective, parallel-group, single-blind randomized controlled trial conducted at Taichung Veterans General Hospital (TCVGH), a tertiary medical center in Taiwan. The study was approved by the Institutional Review Board (IRB) of TCVGH (CE22225A) on 25 May 2022, and registered at ClinicalTrials.gov (NCT05401240) on 29 May 2022. Eligible patients were identified during hospitalization for ACS. Screening, informed consent, and random allocation were completed before discharge. All clinical care followed contemporary ACS and chronic coronary disease guidelines [7,8,13]. The study intervention did not restrict or delay any indicated diagnostic tests or treatments.

The trial protocol was developed in line with the SPIRIT 2025 recommendations for randomized trial protocols [39] and the conduct and reporting of this study will follow CONSORT guidelines for randomized controlled trials. Patient recruitment began in September 2023 at TCVGH and is currently ongoing. The schematic enrollment, interventions, and assessments flowchart is demonstrated in Figure 1.

### 2.2. Participants

Patients are eligible if they meet all of the following criteria:Aged at least 18 years.Hospitalization with a primary diagnosis of ACS, including S-T elevated myocardial infarction (STEMI), non-ST elevated myocardial infarction (NSTEMI), or unstable angina, managed with standard evidence-based therapy.Planned post-discharge follow-up at the cardiology outpatient department (OPD) of TCVGH.Able to understand the study information and provide written informed consent.

Patients are excluded if they meet any of the following criteria:Severe medical complications during hospitalization resulting in a length of stay (LoS) longer than 14 days, such as respiratory failure or acute kidney injury requiring intensive treatment.Undergoing open-heart surgery during the index hospitalization.Contraindications to CPET according to contemporary standards [31].Severe functional dependence with inability to ambulate independently in daily life due to neurological or musculoskeletal conditions.Any other condition judged by the clinical team to make participation unsafe or infeasible.

### 2.3. Interventions

All participants will receive standardized in-hospital education delivered by trained staff. The education covers the goals and components of cardiac rehabilitation, the benefits of regular physical activity, basic home exercise recommendations, medication adherence, and risk factor management. Before discharge, the research team will schedule a first visit at the rehabilitation clinic within approximately 30 days after discharge for all enrolled patients, and this appointment will be documented in the discharge summary. The selection of attendance within 30 days of hospital discharge is based on evidence that earlier scheduling within the first few weeks is associated with higher initial participation, while scheduling beyond one month is linked to lower uptake [40,41].

Patients in the CPET announcement group (intervention arm) will receive the standard education supplemented by a specific behavioral strategy. The research team will formally announce that a CPET would be arranged at their first rehabilitation outpatient visit. The educator uses a standardized script to emphasize that CPET would assess their current cardiopulmonary fitness, compare it with age-matched norms, and guide the intensity of subsequent exercise training. Patients are given a one-page leaflet describing the CPET procedure, safety measures, and clinical benefits in simple language. The discharge instructions explicitly note “rehabilitation clinic visit and cardiopulmonary exercise testing” to reinforce the expectation.

In the standard care group (control arm), patients will receive the same standard education and pre-scheduled rehabilitation clinic appointment, but CPET will not be proactively mentioned during hospitalization.

Ethically, the intervention is defined strictly as the “pre-discharge declaration” and the provision of informational materials. Access to clinical services remains equitable; physicians in both arms retain full discretion to order CPET based on clinical indications post-discharge.

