### 2.4. Randomization, Allocation Concealment and Blinding

A computer-generated random sequence with a 1:1 allocation ratio will be prepared by a statistician not involved in recruitment or outcome assessment. Sequentially numbered, opaque, sealed envelopes containing group assignments are used to ensure allocation concealment. After an eligible patient provides written informed consent and baseline data are collected, the educator opens the next envelope to reveal the assignment and deliver the appropriate intervention.

Outcome assessors and data analysts are blinded to group allocation. Complete blinding of outpatient clinicians is not feasible because some patients in the intervention group might spontaneously mention the planned CPET during follow-up, but clinicians are not informed of group assignment by the study team and are instructed not to seek this information.

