### 2.5. Outcome and Covariates

The primary outcome is their attendance at the rehabilitation clinic within 30 days of hospital discharge. Attendance is defined as completion of at least one scheduled rehabilitation outpatient visit during this period at TCVGH. Attendance is verified via the hospital’s electric medical record system. Given the study’s focus on institutional workflow integration, visits to external facilities are not counted toward the primary endpoint to maintain data consistency.

Secondary outcomes include the following:Cardiac rehabilitation program participation: completion of a predefined early rehabilitation course within 12 weeks after discharge, defined as attending at least six supervised rehabilitation sessions.CPET completion: whether a CPET is ultimately performed during follow-up, irrespective of group.Safety: occurrence of adverse events potentially related to exercise or rehabilitation during the observation period, such as syncope during exercise sessions, sustained arrhythmias requiring urgent management, or emergency department visits or rehospitalization that related to therapeutic exercise

We will also collect the following covariates and potential determinants:Demographic factors—age, sex, body mass index (BMI).Socioeconomic and lifestyle factors—education level, employment and physical workload, physical activity level prior to ACS, and current smoking status.Social context—residential distance from the hospital and whether a family member accompanied the patient during hospitalization.Comorbidities—hypertension, diabetes mellitus, dyslipidemia, and renal impairment.ACS characteristics—ACS type based on electrocardiographic (ECG) findings (STEMI or NSTEMI), peak creatine kinase (CK) level, left ventricular ejection fraction (LVEF) by ECG, and hospitalization LoS.

In addition, to assess key behavioral constructs referenced in the theoretical framework, cardiac self-efficacy will be measured at baseline using the validated Cardiac Self-Efficacy Scale (CSES). The CSES is a disease-specific instrument designed to evaluate patients’ confidence in managing symptoms, maintaining physical function, and engaging in recommended health behaviors following cardiac events [42]. The questionnaire will be administered at the time of hospital discharge, prior to randomization. Higher scores indicate greater perceived self-efficacy related to cardiac disease management.

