### 2.7. Statistical Analysis

All analyses will follow the intention-to-treat principle, and all randomized patients will be included in the primary analysis. Continuous variables are presented as means and standard deviations, and categorical variables as counts and percentages. Baseline characteristics are compared between groups using independent-samples *t* tests for continuous variables and chi-square tests for categorical variables.

For the primary outcome, participants who are lost to follow-up or whose attendance at the rehabilitation clinic cannot be confirmed through the electronic medical record system within the predefined 30-day window will be classified as non-attendees. The proportion of attendees between groups will be compared using the chi-square test, with crude odds ratios and 95% confidence intervals reported. A multivariable logistic regression model will then be fitted to estimate adjusted odds ratios (AORs) with 95% confidence interval for the effect of the intervention on attendance, adjusting for a prespecified set of clinically relevant covariates, including age, sex, ACS type (STEMI vs. NSTEMI), residential distance from the hospital, and baseline physical activity level, as these variables have been linked to cardiac rehabilitation referral/enrolment patterns or post-discharge health behaviors in patients with ACS [15,45,46].

In addition, a broader set of demographic, socioeconomic, clinical, and disease-related variables will be examined in secondary and exploratory analyses to further characterize factors associated with rehabilitation attendance: BMI; education level; employment and physical workload; smoking status; family accompaniment during hospitalization; comorbidities (hypertension, diabetes mellitus, dyslipidemia, and renal impairment); ACS-related characteristics, including peak CK level, LVEF, and LoS; and CSES score. Where appropriate, effect modification by key patient and clinical characteristics will be explored by including interaction terms between the intervention and selected variables.

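### The booking window for the first visit is looser than the 30-day endpoint window, so a kept appointment can be scored as non-attendance

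*Protocol article*

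**What the plan says.** Section 2.3 (Interventions) has the research team make the booking before discharge: "the research team will schedule a first visit at the rehabilitation clinic within approximately 30 days after discharge for all enrolled patients". The date goes into the discharge summary. No latest permissible date is given.

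Section 2.5 (Outcome and Covariates) fixes the endpoint: "The primary outcome is their attendance at the rehabilitation clinic within 30 days of hospital discharge". It adds: "Attendance is defined as completion of at least one scheduled rehabilitation outpatient visit during this period at TCVGH". Section 2.7 (Statistical Analysis) closes the definition. Patients lost to follow-up, and those whose attendance "cannot be confirmed through the electronic medical record system within the predefined 30-day window will be classified as non-attendees", count against their arm. No visit tolerance appears anywhere.

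On the arms, section 2.3 says of the intervention group: "The research team will formally announce that a CPET would be arranged at their first rehabilitation outpatient visit". Of the control group it says that "patients will receive the same standard education and pre-scheduled rehabilitation clinic appointment", without mention of the test. Section 2.4 places allocation after consent and baseline data, when "the educator opens the next envelope to reveal the assignment and deliver the appropriate intervention". The order of booking and envelope opening is not stated.

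**The concern.** The primary outcome is meant to show whether the announcement makes patients come. Whether a kept visit can count also depends on a date that the study team chooses. A patient booked for day 32 who attends on day 32 has done what the plan asks, yet is scored the same as one who never came, unless another scheduled visit falls inside the window.

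Two consequences need to be kept apart:

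- **Late bookings equally common in both arms.** Both attendance proportions shrink by the same factor. The absolute difference shrinks with them and power falls, but no false effect is created.
- **Booking dates that differ by arm.** The comparison then partly reflects booking practice, and the bias can go in either direction. A larger sample does not remove it.

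The first follows directly from the stated rules once any booking falls late. The second needs a further condition that the article does not establish.

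**Working it through.** **1. The rules side by side.**

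| Step | Section | Limit |
|---|---|---|
| Booking the first visit | 2.3 | about 30 days, no upper bound |
| Visit counts as attendance | 2.5 | within 30 days |
| Otherwise non-attendee | 2.7 | predefined 30-day window |

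A booking on day 31 or shortly after is compatible with the first row and fails the other two.

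**2. Inputs from section 2.6.** Intervention rate 25% and a 15-point gain, hence control 10%; two-sided alpha 0.05; power 80%; 100 per group; at least 220 to be enrolled, so about 110 per arm. Section 2.7 analyses everyone randomized and uses a chi-square test.

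**3. The plan's own figure.** With p̄ = (0.10 + 0.25)/2 = 0.175 and d = 0.15:

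n = [1.96·√(2·p̄·(1−p̄)) + 0.8416·√(p1(1−p1) + p2(1−p2))]² / d²

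= [1.96·0.5374 + 0.8416·0.5268]² / 0.0225 = 99.5, so 100 per group.

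The stated sample size reproduces. Power at n per arm is

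Φ{[d − 1.96·√(2p̄(1−p̄)/n)] / √[(p1(1−p1) + p2(1−p2))/n]},

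which gives 80.2% at 100 and 83.8% at 110.

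**4. Late bookings equally common in both arms.** Let f be the share of otherwise counted visits that fall after day 30. The documents do not give f; the values below are assumptions. Each rate is multiplied by (1 − f).

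| f | Control | Intervention | Difference (points) | Power, 100/arm | Power, 110/arm |
|---|---|---|---|---|---|
| 0 | 10% | 25% | 15.0 | 80.2% | 83.8% |
| 5% | 9.5% | 23.75% | 14.25 | 77.7% | 81.5% |
| 10% | 9% | 22.5% | 13.5 | 74.9% | 78.9% |
| 20% | 8% | 20% | 12.0 | 68.9% | 73.0% |
| 30% | 7% | 17.5% | 10.5 | 62.1% | 66.3% |

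Worked line, f = 10% and n = 100: p̄ = 0.1575; [0.135 − 1.96·0.0515]/0.0506 = 0.67; Φ = 0.749.

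**5. Late bookings in one arm only (hypothetical).** With 10% late in the intervention arm alone, the rates are 10% and 22.5%, a difference of 12.5 points, with power 67.1% at 100 per arm and 71.3% at 110. With 20% late in the control arm alone, the difference is inflated to 25 − 8 = 17 points. With no true effect and 20% late in one arm only, the two-sided rejection rate at 100 per arm is about 7.8% if true attendance is 10%, and about 13.5% if it is 25%, instead of 5%. These lines show what a difference by arm would do. They are not evidence that one exists.

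**The case against.** The strongest reply is that the intent is plain. Section 2.3 goes on to justify the 30-day choice by noting that scheduling beyond a month goes with lower uptake, so the team presumably means to book inside the window. Detailed booking rules may sit in the full protocol. This lowers the likely share of late bookings. It does not resolve the wording, because the article states both limits and they do not match.

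A reader might infer that the comparison is biased because unblinded staff choose the dates, or because intervention dates must wait for an exercise-test slot. The documents do not support that. Section 2.3 describes booking for all enrolled patients before it separates the arms, gives controls the same pre-scheduled appointment, and confines the intervention to the announcement and leaflet. No section describes reserving a test slot, limited test capacity or a clinic date chosen around the test. What remains is narrower: the order of booking and allocation is unstated, and section 2.4 blinds outcome assessors and data analysts but does not mention those who book.

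A reader might also infer that the trial is underpowered. That does not follow either. Section 2.6 sized the trial for 30-day attendance, so 10% and 25% can be read as rates already net of late visits, in which case the reduction in the table does not apply. At the enrolment target there is also some reserve: with 10% late in both arms, power is 78.9%, close to the planned 80%.

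**Conclusion.** The mismatch is real, concerns the primary endpoint, and is not resolved elsewhere in the article. Under the stated rules a kept appointment can be scored as a failure.

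Its size cannot be derived, because the share booked after day 30 is not given. If that share is zero, nothing is lost. If it is 10% or 20% in both arms, power falls from 80% to about 75% or 69% at 100 per arm, and from 84% to about 79% or 73% at 110. These figures assume that 10% and 25% are rates before any lateness.

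Bias between the arms is a possibility that the documents leave open, not something they show. The sample size calculation itself is correct. Severity is moderate: worth correcting while recruitment continues, but not a defect that invalidates the design.

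**What to change.** 1. Reconcile sections 2.3, 2.5 and 2.7 so that no booked date can lie outside the window that defines the endpoint.
2. For patients still to be enrolled, set and record the appointment date before the envelope is opened, and say so in section 2.4.
3. For all patients, report the booked day after discharge by arm. Section 2.3 already has the appointment documented in the discharge summary, which should supply the dates for patients already enrolled.
4. Before unblinding, prespecify one sensitivity analysis of attendance at the first booked appointment whatever its date. Leave the primary analysis unchanged.

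The cost is protocol wording, a small change in the order of steps at discharge, and extraction of booked dates. The downside is that the reordering comes mid-recruitment (section 2.1 gives a September 2023 start) and cannot alter dates already booked. For those patients, items 3 and 4 are the only remedy.
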